#### Adherence

Participants will be asked to record their adherence (i.e. days per week, hours per day) to their assigned compression therapy treatment in a daily journal. Treatment-specific outcomes such as the time required for administration of night-time compression, reasons for removal of the garment at night and independence/assistance in application will be included in the diary. Participants will be asked to return the completed diary for each respective 6-week time period at the subsequent follow-up visit. We will also record any additional appointments required to teach CB or to assess wear/fit of the NCSG.

### Adverse events

*Adverse events* related to the application of compression (i.e. skin breakdown or reaction, such as rash) will be recorded. Any *adverse events* related to the condition of lymphedema (i.e. infection/cellulitis or blood clot in the arm) will be verified with the participant’s physician. If this occurs, as per standard care, treatment with compression will be stopped until deemed safe to resume by the physician. We will also record any relapses in arm lymphedema volume (>50 %) that require more intensive reduction treatment.

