### Blinding

At each measurement point starting after the baseline assessment through the RCT portion of the trial (i.e., 6 week and 12 week follow-ups), an Independent Assessor unaware of treatment allocation (blinded) will perform the measurements of arm volume using the perometer, bioimpedance analysis, and body weight. The Independent Assessor will also administer the outcome measures for sleep disturbance, self-efficacy, and quality of life. The Adherence Diary will be collected by the Research Coordinator at each follow-up visit. Follow-up sessions will take place in the respective rehabilitation department and each session will take 30 to 45 min to complete. Blinding of participants and practitioners will not be possible as participants are aware of the compression therapy treatment they are receiving. Study garments will be purchased at cost from participating industry partners through the grant funds. In the event that a study participant is unable to continue with their assigned treatment, they will remain in their randomized group to preserve the intention-to-treat principle. Study participants will be free to withdraw at any time but will be invited to continue to attend for scheduled follow-ups for the duration of the study.

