### Statistical analyses

Baseline medical and demographic characteristics, arm dominance relative to the lymphadematous arm, and adverse events of the three groups will be compared using one-way ANOVA for continuous data and Pearson’s Chi-square tests for categorical data. The primary analysis will compare the groups with regard to percent excess lymphedema volume and quality of life at 12-weeks using a one-way ANOVA. General linear models will be used to adjust for centre and lymphedema category (mild or moderate), and to evaluate the treatment effect in subgroups defined by the strata. Sleep quality, self-efficacy, and adherence-related outcomes will be analyzed by repeated measures modeling and one-way ANOVA on change scores.

Descriptive data on accrual rates will include the number of women screened for eligibility, the number eligible, the number agreeing to participate, and reasons for refusal to participate. Data on adherence will be collected from all women throughout the 24-week study period. Adherence data will include days worn per week and hours worn per 24-h period, as appropriate, for each of the following: 1) NCSG; 2) CB; 3) day-time compression sleeve. We will also examine adherence during weeks 13 to 24 to the newly assigned NCSG for the standard care and standard care + CB groups, and ongoing adherence during weeks 13 to 24 in the originally assigned standard care + NCSG group. Analyses of primary outcomes will be performed at the end of the RCT portion of the trial. Within group analyses will also be conducted for primary and secondary outcomes from weeks 13 to 24 following completion of all follow-up measures.

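### Skin events are recorded only as related to compression, which leaves the planned three-group adverse event comparison open to ascertainment bias

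*Protocol article*

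**What the plan says.** The Adverse events section of the protocol article has three capture rules.

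- Skin events: those "related to the application of compression (i.e. skin breakdown or reaction, such as rash) will be recorded".
- Infection or clot: events "related to the condition of lymphedema (i.e. infection/cellulitis or blood clot in the arm) will be verified with the participant’s physician".
- Relapse: "We will also record any relapses in arm lymphedema volume (>50 %) that require more intensive reduction treatment".

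No category covers affected-arm events regardless of cause. The section does not say who records events or who decides that one is related.

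The Blinding section says that the independent assessor, who is unaware of allocation, "will perform the measurements of arm volume using the perometer, bioimpedance analysis, and body weight", and also administers the questionnaires. Adverse events are not on that list. The same section says: "Blinding of participants and practitioners will not be possible as participants are aware of the compression therapy treatment they are receiving".

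The Adherence section gives every participant a diary. It adds that "reasons for removal of the garment at night and independence/assistance in application will be included in the diary", and that additional appointments for bandage teaching or garment fit will be noted.

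The Statistical analyses section commits to a formal comparison: "adverse events of the three groups will be compared using one-way ANOVA for continuous data", with Pearson chi-square tests for categorical data.

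**The concern.** In a randomized comparison, the difference between arms is itself the evidence that events are caused by treatment. If an event must first be attributed to compression before it is counted, the expected answer can enter the data before the test is run. Compression is also exactly what differs between the groups. Standard care participants wear only their own fitted sleeve, while the other two groups begin a new night-time exposure. A new rash may be put down to a new bandage or garment more readily than to a sleeve already in use. The opposite is also possible: staff may discount reactions to a device they fitted.

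Chances to notice an event may differ too, because unscheduled teaching and fitting appointments in weeks 1 to 12 concern only the two night-compression groups.

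At stake is whether the planned three-group test means anything. Events never written down cannot be recovered by a later analysis plan. The statement under Progress to date that no adverse events had occurred among 39 randomized women shows the difficulty: under this rule it could mean that there were no events, or that none was judged related.

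**Working it through.** The document gives no adverse event rate, attribution rate or power for safety, so there is no figure of the plan to reproduce. The check has two parts.

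**1. The sections side by side**

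| Element | Same in all arms? |
|---|---|
| Day-time sleeve, so compression-related events are possible (Groups 1–3) | Yes |
| Scheduled visits at weeks 6 and 12 (Groups 1–3, Recruitment) | Yes |
| Core adherence diary (Adherence) | Yes |
| New night-time exposure to which a skin event can be attributed (Groups 2 and 3) | No, night arms only |
| Diary item on reasons for removal at night (Adherence) | Not applicable to standard care in weeks 1–12 |
| Extra teaching or fitting appointments (Adherence) | No, night arms only in weeks 1–12 |
| Recording assigned to the blinded assessor (Blinding) | Not listed for any arm |

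The wording of the rule is the same in every arm. The conditions under which it is applied are not.

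**2. What unequal capture would do (illustration; every rate is assumed)**

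The recorded rate in an arm is true risk × capture probability.

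- Spurious excess: with a true risk of 10 % in every arm, capture of 90 % in a night arm and 40 % in standard care, the recorded rates are 0.10 × 0.90 = 9 % and 0.10 × 0.40 = 4 %. The ratio is 9/4 = 2.25. With 40 women per arm (Sample size section), that is 3.6 against 1.6 women.
- Hidden excess: with true risks of 20 % in a night arm and 10 % in standard care, and half of the night-arm events discounted, the recorded rate is 0.20 × 0.50 = 10 % against 10 %. A true ratio of 2 disappears.

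The effect on the planned test was simulated. The count in arm i is x_i ~ Binomial(40, p × c_i), with the same true risk p in all arms, c = 1 in both night arms, and c = 1, 0.75 or 0.50 in standard care. With e = (x_1 + x_2 + x_3)/3, the 3 × 2 Pearson statistic is Σ(x_i − e)²/e + Σ(x_i − e)²/(40 − e). It is compared with the 5 % point of chi-square on 2 degrees of freedom, −2 ln 0.05 = 5.99. There were 200,000 replicates per cell.

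| True risk, all arms | Equal capture | Standard care at 75 % | Standard care at 50 % |
|---|---|---|---|
| 10 % | 4.4 % | 5.7 % | 10.2 % |
| 20 % | 4.9 % | 8.0 % | 20.7 % |
| 30 % | 5.0 % | 11.0 % | 34.6 % |

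The entries are the proportions of trials that declare a difference although the true risks are equal. With equal capture the test holds its level. With unequal capture it does not, and the distortion grows with both the event rate and the imbalance.

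**The case against.** The case against has force on several points.

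- A reader might infer that unblinded staff judge relatedness. The document names no recorder and no judge. The duties of the coordinator-therapist in Trial management include teaching bandaging, fitting garments and helping with data collection, but not attribution. Infection and clot events are verified with the participant's own physician. What stands is narrower: no blinded person is given the task.
- A reader might infer that the diary is how events are found, and that it favours the night arms. The Adherence section describes an adherence record kept by everyone and never calls it a source of adverse events. Of the night-specific items named, only reasons for removal could plausibly reveal one. The diary is at most a minor support.
- Every arm wears a sleeve and has the same scheduled visits, so a compression-related event can be recorded in any of them. This reduces the imbalance but does not remove it.
- The bracketed examples in the skin-event rule could be read as naming event types rather than imposing a causal test. The sentence still ties recording to relatedness and offers no all-cause alternative.
- Elicitation procedures and form fields may sit in the full protocol, case report forms or operating procedures, so their absence from an article is no finding. The point does not rest on that absence. It rests on the stated rule combined with the stated comparison.
- Adverse events appear in no hypothesis, objective or endpoint list. This limits the importance of the point, but the three-group comparison is still planned.

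**Conclusion.** The point holds in limited form. Capture of skin events is conditioned on attribution to compression, recording is not among the blinded assessor's listed tasks, and the events so captured are to be compared across groups that differ in compression. The comparison is open to ascertainment bias that could not be repaired afterwards.

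A reader might go further and conclude that the comparison is biased, or that the trial can say nothing about safety. The documents do not support that. Direction and size depend wholly on attribution and event rates that are not given. The illustrated rejection rates, from 5.7 % to 34.6 % under unequal capture, rest on assumed true risks of 10 % to 30 % and assumed relative capture of 75 % or 50 % in standard care, and the distortion could equally run the other way. The volume and quality-of-life results are untouched. This is a cheap improvement to a subsidiary comparison.

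**What to change.** 1. **Adverse events.** Record every new skin, infection or clot event in the affected arm, in all three groups, whatever the suspected cause. Keep relatedness to compression as a separate field that does not decide inclusion. Physician verification and relapse recording can stay as they are.
2. **Elicitation.** Ask one identically worded question about the affected arm in all three groups at the existing week 6 and week 12 visits, and print the same item in every participant's existing diary.
3. **Statistical analyses.** Base the between-arm comparison on all such events over the same 12-week randomized window in each arm. The window needs a common definition: the NCSG group waits for its garment, while the Recruitment section times visits from the start of the assigned intervention. Describe events in weeks 13 to 24 within group only, because both comparison groups have by then moved to the NCSG.

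The cost is one question, one diary line and one form field at visits already planned. More minor, unrelated events will be listed. Women already enrolled (39 randomized by September 2015) have data under the old rule, so the report should state when the change took effect. Nothing here alters clinical management.

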### Allocation concealment and method of randomization

Participants will be randomized in a 1:1:1 ratio to Standard Care, CB or NCSG using a secure central randomization service administered by the Clinical Trials Unit of the Cross Cancer Institute.

### Blinding

At each measurement point starting after the baseline assessment through the RCT portion of the trial (i.e., 6 week and 12 week follow-ups), an Independent Assessor unaware of treatment allocation (blinded) will perform the measurements of arm volume using the perometer, bioimpedance analysis, and body weight. The Independent Assessor will also administer the outcome measures for sleep disturbance, self-efficacy, and quality of life. The Adherence Diary will be collected by the Research Coordinator at each follow-up visit. Follow-up sessions will take place in the respective rehabilitation department and each session will take 30 to 45 min to complete. Blinding of participants and practitioners will not be possible as participants are aware of the compression therapy treatment they are receiving. Study garments will be purchased at cost from participating industry partners through the grant funds. In the event that a study participant is unable to continue with their assigned treatment, they will remain in their randomized group to preserve the intention-to-treat principle. Study participants will be free to withdraw at any time but will be invited to continue to attend for scheduled follow-ups for the duration of the study.

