**Fig. 3 Fig3:**
[figure not shown]
Study schema

The randomized fast-track trial (with delayed assignment to NCSG for both comparison groups) is seen as a more acceptable design to patients, families and staff, given that the majority of eligible participants will have a strong preference for assignment to the NCSG group. Moreover, we feel this design, which was used in the pilot study, will optimize recruitment and retention of the comparison group participants in the trial.

The follow-up period after the intervention (weeks 13 to 24) will follow a longitudinal observational design and provides an opportunity to examine factors related long-term adherence to night-time compression.

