### Sample size for randomized fast-track trial phase

The sample size required per group to detect at least a minimal clinically important mean difference of 20 % (SD ±25) in arm lymphedema volume in favor of either the standard care + NCSG, standard care + CB group and standard care alone is 36 participants. A total sample of 108 participants will achieve a power of 86 % with a significance level of 0.05 using a one way ANOVA test. The sample size required per group to detect at least a minimal clinically important difference on the Lymph-ICF quality of life scale of 15 points out of 100 (SD ±22) between the standard care + CB group and the standard care + NCSG group is 36 participants. A total sample of 108 will achieve a power of 80 % with a significance level of 0.05 using a two-sided Mann-Whitney test assuming the actual distribution is normal. To allow for an estimated 10 % loss to follow-up and non-compliance/cross-over of the standard care group, we will recruit an additional 12 patients for a total of 120 participants (40 participants in each of the three treatment groups).

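### The primary one-way ANOVA at week 12 drops women without a week-12 measurement and ignores week-6 data, so uneven loss could bias the contrast

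*Protocol article*

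**What the plan says.** All places are in the protocol article.

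- **Statistical analyses.** The primary analysis compares the groups "with regard to percent excess lymphedema volume and quality of life at 12-weeks using a one-way ANOVA". General linear models then adjust for centre and lymphedema category. For other outcomes the same section chooses differently: "Sleep quality, self-efficacy, and adherence-related outcomes will be analyzed by repeated measures modeling and one-way ANOVA on change scores".
- **Blinding.** If a woman cannot continue her assigned treatment, "they will remain in their randomized group to preserve the intention-to-treat principle". Women who withdraw "will be invited to continue to attend for scheduled follow-ups for the duration of the study". Participants and practitioners are not blinded. The assessor is blinded at weeks 6 and 12.
- **Sample size.** The arm-volume target is a "minimal clinically important mean difference of 20 % (SD ±25) in arm lymphedema volume", with 36 women per group. To allow for 10 % loss and non-compliance or cross-over, "we will recruit an additional 12 patients for a total of 120 participants".
- **Methods/Design, text after the study schema.** Most eligible women are expected to prefer the garment strongly. Both comparison groups are offered it after week 12, and the authors expect that this design "will optimize recruitment and retention of the comparison group participants in the trial".
- **Abstract and Recruitment.** Measurements are taken at baseline and at weeks 6, 12, 18 and 24.

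**The concern.** A one-way ANOVA on a single visit needs a value at that visit. A woman seen at baseline and week 6 but not at week 12 contributes nothing, and the general linear models for centre and severity have the same limit. The Abstract words the primary outcomes as differences from baseline to week 12. If that is the variable analysed, baseline enters, but the woman without a week-12 value still drops out and week 6 is still unused.

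This matters when the women who are missing differ from those who stay, and differ by arm. Here the treatment is open and one arm is the expected favourite. If women on standard care whose arms are worsening stop attending, the remaining standard-care mean looks too good and the night-time effect is understated. If women struggling with bandaging stop attending, the bandaging arm looks too good instead. The week-6 visit would often show which women these were, and the stated test does not look at it.

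**Working it through.** **1. The plan's own figures.** For arm volume, take three groups of 36, SD 25 and means 0, 10 and 20. The noncentrality is 36 × (10² + 0² + 10²)/25² = 11.52 on 2 and 105 degrees of freedom, and power is 0.859 (stated 86 %). For Lymph-ICF, take 15 points, SD 22 and 36 per group, with the Mann-Whitney efficiency 3/π applied to n. Power is 0.796 to 0.807 (stated 80 %). For recruitment, 108/0.9 = 120 (as stated). All three reproduce.

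**2. Inputs for the bias check.** From the Sample size section: SD 25 and a true difference of 20. The rest are assumptions, because the documents give no loss by arm, no correlation between visits and no loss mechanism:
- week 6 to week 12 correlation ρ = 0.8
- 5 % loss at random in each night-time arm
- in standard care, probability of loss p(Z) = 1/(1 + exp(2.2 − sZ)), where Z is the standardised week-6 value (higher is worse) and s sets the strength of selection.

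**3. Formula.** Among women who stay, the standard-care mean at week 12 moves by −ρ × SD × E[Z p(Z)]/(1 − p̄), where p̄ is the mean loss. Random loss in the other arms moves nothing.

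| Selection in standard care | p̄ | E[Z p(Z)] | Shift (points) | Observed-case difference |
|---|---|---|---|---|
| none (s = 0) | 0.100 | 0 | 0 | 20.0 |
| mild (s = 0.5) | 0.109 | 0.047 | 20 × 0.0472/0.891 = 1.1 | 18.9 |
| moderate (s = 1.0) | 0.134 | 0.103 | 20 × 0.1031/0.866 = 2.4 | 17.6 |
| steep (s = 1.5) | 0.168 | 0.161 | 20 × 0.161/0.832 = 3.9 | 16.1 |

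The factor 20 is 0.8 × 25. If standard-care loss is held near 10 %, mild and moderate selection give about 1.0 and 1.9 points. In the steep case overall loss is (16.8 + 5 + 5)/3 = 8.9 %, inside the plan's 10 %, but it comes mostly from standard care.

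**4. Sensitivity to the correlation.** The shift is proportional to ρ. In the steep case, ρ = 0.7, 0.6 and 0.5 give 3.4, 2.9 and 2.4 points.

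**5. Cross-check without a selection model.** Put all 12 allowed losses in the two comparison arms (6 of 40, or 15 %, each) and none in the garment arm. If the lost women differ from those observed by 10, 20 or 25 points, the bias is 0.15 × 10 = 1.5, 0.15 × 20 = 3.0 or 0.15 × 25 = 3.75 points. Equal loss with the same mechanism in every arm gives 0.

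**6. What the earlier visits recover.** Simulated trials of the steep case (40 per arm; correlations 0.6 for baseline with week 6 and 0.5 for baseline with week 12) give an observed-case difference of 16.1 to 16.3. Predicting missing week-12 values from baseline and week 6 gives 19.9 to 20.1. This recovery is built in, because loss was made to depend only on the week-6 value.

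**7. Quality of life.** On the same standardised scale the steep case moves an arm mean by 3.9 × 22/25 = 3.4 points, against the 15-point target. That target compares bandaging with the garment, so the selective loss would have to be in the bandaging arm.

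**The case against.** A reader might infer more than this: that the plan contradicts its own intention-to-treat claim, and that sizing on 108 shows a completers' analysis. The documents do not support either reading. The intention-to-treat sentence is about women who stop treatment, not women who miss visits. They are kept in their group, and women who withdraw are still invited to attend. No passage defines a completers' set or excludes anyone. Going from 108 to 120 is ordinary inflation for loss. The 10 % also covers non-compliance and cross-over, so it is not a count of women absent from the analysis.

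Three further objections have weight:

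- A statistical analysis plan that is not shown may contain a missing-data rule, and naming an ANOVA does not rule out imputing first. That stands, so the absence of such a rule is no finding. What remains is the choice the article does make: a single-visit test for the primary outcomes beside repeated-measures modelling for secondary ones.
- The delayed garment gives comparison-arm women a reason to stay to week 12. That stands too. It makes selective loss less likely, although the plan still budgets for loss.
- The larger bias figures need steep selection and more than three times the loss in standard care (16.8 % against 5 %). That is correct, and it is why a range is given.

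**Conclusion.** The point holds as a weakness in the stated primary test. Taken literally, the one-way ANOVA at week 12 leaves out women not measured then and makes no use of week 6, in an open trial where one arm is strongly preferred. Bias from this is possible but not established. Under the assumptions above it is 0 points without selection, about 1 to 2 points with mild to moderate selection, and about 4 of 20 points with steep selection in standard care. Its direction depends on who leaves. A reader might conclude that the effect will be understated. The documents do not show that, because they report neither loss by arm nor any link between loss and outcome. The intention-to-treat statement and the sample size can stand.

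**What to change.** Make the primary analysis a longitudinal model on all randomised women, with baseline, week 6, week 12, arm, centre and lymphedema severity, and take the week-12 contrast between arms as the primary estimate. Multiple imputation of missing week-12 values from the same variables would serve equally well. Apply it to both percent excess volume and Lymph-ICF. Add one delta-shift sensitivity analysis that worsens the imputed values by arm. Keep the one-way ANOVA as a supporting analysis, labelled observed-case. If the unseen analysis plan already does this, it is enough to align the wording of the Statistical analyses section.

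The cost is plan wording and a little more programming, since baseline and week-6 values are already collected. The downside is reliance on a missing-at-random assumption, which the delta-shift analysis is there to probe.
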